#### C. Recruitment of participants:

Patients and/or visitors of the hospital will be screened for tobacco use. Those who are known tobacco smokers will be advised to register for cessation services at the tobacco cessation center. The smoking cessation trial aims to recruit 490 participants in each arm. The participants will be enrolled based on the eligibility (all current smokers aged 18 years and above with a motivation to quit). Before randomization, smokeless tobacco users, smoking frequency of less than 10 cigarettes per day, pregnant women, lactating women, patients with recent history of myocardial infarction of less than 3 months, and electronic cigarette users will be excluded from the study. Further to this, randomization will be done to allocate participants to the appropriate study arms. The participant information sheet will be given and explained to the participants by the investigator about the risks and benefits of participating in the trial.

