Carbon monoxide (CO) monitor will be used to assess the exhaled CO level of the study participants during each visit. The cutoff point will be six parts per million or less for nonsmokers and more than six parts per million for smokers [15]. Cotinine is a metabolite of nicotine with a long half-life (15–19 hours) that can be measured in body fluids such as saliva, urine and plasma. Measurement of salivary cotinine as an indicator of tobacco use, exposure to secondhand smoke or use of pharmaceutical nicotine is commonly used in population studies, given the ease of sample collection and minimal discomfort to study subjects.[13]. Hence, saliva cotinine test will be done to assess the smoking status of the participants during baseline and end-line of the study. Saliva cotinine test results will be considered as the biochemical verification for smoking status. However, carbon monoxide levels will be a complementary test to support the evidence for smoking status of the participants. This is because the concentration of cotinine measured in plasma, saliva, or urine has the highest sensitivity and specificity to detect smokers in comparison to CO concentration in blood and expired air due to relatively lower sensitivity than cotinine [14]

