| Health related quality of life                                           | 0-Day, 6 months, 12 months                                                                                                                                                                                                                                                                                                                   | 0-Day, 6 months, 12 months                                                                                                                                                                                                                                                                               |
| Saliva cotinine test                                                     | 0-day, Month- 3, 6, 12                                                                                                                                                                                                                                                                                                                       | 0-day, Month- 3, 6, 12                                                                                                                                                                                                                                                                                   |

**K.Statistical Analysis:** The collected information will be summarized by using frequency and percentage for qualitative data, mean and standard Deviation for quantitative data. To compare the outcome measures, quantitative before and after intervention, paired-t test will be used. If data is not following normal distribution, Wilcoxon Signed Rank test will be used. To compare qualitative outcomes, Chi-square test or Fischer exact test will be used. To compare the difference in outcome measures between two intervention groups, independent sample 't' test will be used. If data is not following normal distribution, Mann Whitney test will be used. The P value less than 0.05 will be considered as statistically significant.

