## Budget justification

As shown in details in Appendix C, the total project cost for three years is categorized as follows.

| ITEM                                                 | FUND (USD) |
|------------------------------------------------------|------------|
| Payment to research team                             | 109200     |
| Travel                                               | 14400      |
| Materials and supplies                               | 228400     |
| Equipment                                            | 14600      |
| Publication costs, registration, dissemination costs | 25000      |
| Subcontracts                                         | 9000       |
| Overheads (5%)                                       | 21084      |
| Total                                                | 421684     |

The justification of each item are as follows:

1) Payment to the research team: Our research team consists of MPH graduates/students from NUSOM, Nazarbayev university. Students & graduates of Nazarbayev university will enhance their knowledge in the field of tobacco control & also, they will research publish papers in this area. The payment at this section will be allocated to students /Graduates during their research.

2) Travel: The travel will cover conference expenses of the Investigators.

3) Equipment: The equipment needed to buy for the project is as follows: Portable spirometers, carbon monoxide monitors, sphygmomanometers, and weighing scale, all two each in numbers will be procured. To establish an office setup, furniture & computers will be procured. All the equipment mentioned will be covered under the fund. spirometer & carbon monoxide monitor estimated at 2000 dollars per unit.

4) Materials & supplies: Nicotine patches in the intervention group will be estimated at 120 patches per participant for 16 weeks; 90 patches per participant in the control group for 12 weeks. Nicotine gums are estimated at 600 gums per participant in both the groups. Four saliva cotinine kits are required for each participant at 0, 3 months, 6 months, and 12 months. All the mentioned materials & supplies will be covered under the fund. Nicotine patch is estimated at 8 dollars per piece & nicotine gums at 0.35 dollars per piece. saliva cotinine test at 8 dollars per piece

5) Publication cost: This section will cover the cost of publication (proof reading, charges for color printing etc.) in high ranked journals, if necessary.

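### The day-0 CO and cotinine results are not tied to eligibility, so nothing prevents a true non-smoker from being randomised and counted as abstinent

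*Protocol*

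**What the plan says.** **Entry.** Protocol section 3.C screens hospital patients and visitors for tobacco use: "Those who are known tobacco smokers will be advised to register for cessation services at the tobacco cessation center". Those enrolled are "all current smokers aged 18 years and above with a motivation to quit". The exclusions begin "Before randomization, smokeless tobacco users, smoking frequency of less than 10 cigarettes per day, pregnant women, lactating women" and go on to recent myocardial infarction and e-cigarette use. No criterion refers to a CO or cotinine value.

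**Tests.** Section 3.D gives a CO rule: "The cutoff point will be six parts per million or less for nonsmokers and more than six parts per million for smokers". It also says that a "saliva cotinine test will be done to assess the smoking status of the participants during baseline and end-line of the study". Cotinine is named there as the biochemical verification of smoking status, with CO as a complementary test of lower sensitivity. No cotinine cutoff is given. The table in section 3.J puts CO on day 0 and at months 1, 3, 6, 9 and 12, and cotinine at "0-day, Month- 3, 6, 12".

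**Outcome and analysis set.** Section 3.E calls a participant non-abstinent when there is self-reported smoking and a positive cotinine test. The Results paragraph after section 3.K commits to intention to treat.

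**The concern.** Cessation can be observed only in someone who smokes at entry. The protocol plans to measure smoking status biochemically on day 0 and, for CO, says which readings mean smoker and non-smoker. It then gives the result no consequence for eligibility, randomisation or analysis. The entry rules that remain, being a known smoker and the number of cigarettes a day, depend on what the person reports, although the protocol does not use that term.

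A true non-smoker who enters has no smoking to report. Once the course of nicotine products is over, that person also has no reason to be cotinine-positive. Under section 3.E this is abstinence at 12 months, whichever arm the person is in, and intention to treat keeps the person in the denominator. At stake are the size of the reported quit rates, the size of the treatment difference, and part of the stated 80% power.

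**Working it through.** **Inputs.** From section 3.G: abstinence 47.5% v 27.5%, two-sided 5% level, 80% power, 91 per arm, raised by 10% to 100. From section 3.C: 490 per arm. The share f of true non-smokers in each arm is an assumption, because the documents give no value; 2%, 5% and 10% are shown.

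**The plan's own figure.** With the pooled-variance formula, no continuity correction and a mean rate of 0.375:

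n = [1.960 × √(2 × 0.375 × 0.625) + 0.842 × √(0.475 × 0.525 + 0.275 × 0.725)]² / 0.20² = 90.8, so 91 per arm. Then 91 × 1.10 = 100.1, as stated. The sample size arithmetic in section 3.G reproduces.

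**Dilution.** If a share f of each arm are non-smokers who all count as abstinent, and the planning rates hold among the true smokers, the rate in each arm becomes p′ = f + (1 − f)p, and the difference becomes (1 − f) × 20 points. For f = 5%: 0.05 + 0.95 × 0.475 = 0.501 and 0.05 + 0.95 × 0.275 = 0.311, a difference of 19.0 points.

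**Power.** This is the exact power of the uncorrected chi-square test, found by summing the binomial probabilities of all outcome pairs that reject. The 100-per-arm column assumes no loss to follow-up. The last column applies the sample size formula above to the diluted rates.

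| f (assumed) | Rates, % | Difference, points | Risk ratio | Power at 91 per arm | Power at 100 per arm | n per arm for 80% |
|---|---|---|---|---|---|---|
| 0 | 47.5 v 27.5 | 20.0 | 1.73 | 80.7% | 83.8% | 91 |
| 2% | 48.6 v 29.0 | 19.6 | 1.68 | 78.5% | 81.9% | 96 |
| 5% | 50.1 v 31.1 | 19.0 | 1.61 | 74.7% | 79.1% | 104 |
| 10% | 52.8 v 34.8 | 18.0 | 1.52 | 68.1% | 74.4% | 119 |

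At 490 per arm, power is about 99.99% even at f = 10%. The raised quit rates and the smaller difference are the same at any sample size.

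**The case against.** The strongest reply is that the protocol is silent here, not wrong. Being a current smoker is already an entry condition, people are screened by a method that is not named, and section 3.D says what a non-smoker's CO reading is. Site staff could reasonably read the two together and turn away someone who tests as a non-smoker. Randomisation would also balance any non-smokers who slip through, so neither arm gains. At f = 2% the loss is about 2 points of power at either 91 or 100 per arm, and at 490 per arm it is negligible.

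Much of this stands. The effect is dilution, it is small when f is small, and f is unknown. But no section states the link between test and entry, and eligibility belongs in the protocol. The gap is also hard to repair later, because removing such people after randomisation would conflict with the intention-to-treat commitment.

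Four stronger readings go beyond the documents:

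- A reader might infer that people who test as non-smokers will in fact be randomised. The order of the day-0 tests and randomisation is not stated; all that can be said is that nothing prevents it.
- A reader might treat anyone at or below 6 ppm as an automatic success. Section 3.D itself calls CO the less sensitive test. A smoker with a low reading may be cotinine-positive throughout and end as non-abstinent.
- A reader might extend the argument to very light smokers. One who goes on smoking, reports it and has positive cotinine is non-abstinent under section 3.E, so the dilution formula covers true non-smokers only.
- A reader might take the budget line "Nicotine patch is estimated at 8 dollars per piece" as a motive to over-report smoking. It is a product cost; nothing in the protocol says that such over-reporting occurs or how often.

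**Conclusion.** The point holds as a gap in the entry rule. The protocol schedules two tests of smoking status on day 0 and attaches neither to eligibility, so a true non-smoker can be randomised, counted as abstinent and kept in the analysis.

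The expected result is higher quit rates in both arms and a difference shrunk by the factor (1 − f), towards no effect. For f between 2% and 10%, power drops by about 2 to 13 points at 91 per arm and by about 2 to 9 points at 100 per arm; at 490 per arm it is essentially unchanged. These figures assume that f is equal in the two arms, that every such entrant is followed up and classed as abstinent, and that the planning rates of section 3.G apply to the true smokers. The protocol should be changed because the remedy uses tests already planned, not because large harm has been shown.

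**What to change.** In section 3.C, state that the day-0 CO reading and saliva sample are taken before the allocation envelope is opened and before any trial product is issued. A person is then randomised only if smoking is confirmed by CO above 6 ppm, the protocol's own smoker cutoff. If CO is 6 ppm or less, confirmation may come from a repeat CO reading or from a positive day-0 salivary cotinine test.

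CO should not be the sole gate. Section 3.D ranks it below cotinine, and it could turn away genuine smokers, such as hospital patients who have not smoked recently. The cotinine cutoff must be stated, because section 3.D notes that cotinine also reflects second-hand smoke and pharmaceutical nicotine.

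Both tests are already scheduled for day 0, and the budget already covers the CO monitors and a cotinine kit for that visit. The cost is a few repeat readings, a few screen failures, kits used on people who are then not randomised, and a short wait for the cotinine result in those with low CO.

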**D. Intervention and Control arm:**

Combining slow-release NRT (the patch) with rapid-release forms (nicotine gum, lozenge, inhaler, or nasal spray) increases the effectiveness of NRT and is comparable with treatment with varenicline. Nicotine replacement therapy is considered safe, including in combination form or if used while smoking. Among the different forms of NRT, adherence is greatest with the patch.[11]. The intervention arm is the combination nicotine replacement therapy. This includes a fixed dose combination of nicotine patch and 4 mg nicotine chewing gum for 12 weeks on tapering dosage pattern. The control arm includes 4 mg nicotine chewing gums alone for 12 weeks on tapering dosage pattern.

Based on the WHO-5As model of brief advice, group counseling (Ask, Advise, Assess, Assist, Arrange) will be arranged for the participants in both the arms to quit in a clear, strong and personalized manner. Then, smokers will be assessed for the readiness of quitting. For those willing to quit, the study team would assist the participants with the interventional quitting plans as per the allocated arm. The frequency of follow up for behavioral support will be arranged every two weeks. Supplementary cessation assistance such as social media and self-help materials will be provided. For those not willing to quit, 5Rs (Relevance, Risks, Rewards, Roadblocks, Repetition) motivational counseling intervention will be provided at least three times with a gap of one week in every group counseling until the participants were ready to quit [12.]

Carbon monoxide (CO) monitor will be used to assess the exhaled CO level of the study participants during each visit. The cutoff point will be six parts per million or less for nonsmokers and more than six parts per million for smokers [15]. Cotinine is a metabolite of nicotine with a long half-life (15–19 hours) that can be measured in body fluids such as saliva, urine and plasma. Measurement of salivary cotinine as an indicator of tobacco use, exposure to secondhand smoke or use of pharmaceutical nicotine is commonly used in population studies, given the ease of sample collection and minimal discomfort to study subjects.[13]. Hence, saliva cotinine test will be done to assess the smoking status of the participants during baseline and end-line of the study. Saliva cotinine test results will be considered as the biochemical verification for smoking status. However, carbon monoxide levels will be a complementary test to support the evidence for smoking status of the participants. This is because the concentration of cotinine measured in plasma, saliva, or urine has the highest sensitivity and specificity to detect smokers in comparison to CO concentration in blood and expired air due to relatively lower sensitivity than cotinine [14]

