When a person stops using tobacco, the aim of NRT is to replace the nicotine that the smoker would have been receiving, without the additional harmful elements of tobacco.[7]. With fast acting drugs such as nicotine gum, the nicotine is absorbed through buccal mucosa and reaches peak plasma nicotine concentrations within 15–30 min (as compared to within 1–2 min after smoking) and the blood levels reach a flat peak after about 30 minutes of chewing [8]. On the contrary, trans-dermal patches release nicotine more gradually with peak concentrations within hours after application [9]. As a result, none of the available NRT products deliver such high doses of nicotine as quickly as cigarettes. One implication is that combination NRT (fast-acting form + patch) results in approximately 15% to 36% higher long-term quit rates than a single form of NRT. [7]

Using a nicotine replacement treatment (or other smoking cessation drugs) before a quit attempt while smoking normally is called preloading. A systematic review showed limited evidence that nicotine preloading may be effective, but with unexplained heterogeneity between studies. Some studies suggested that nicotine preloading doubled the likelihood of achieving abstinence, while other studies suggested that preloading had no effect [10]. However, more evidence is needed to determine the effectiveness of preloading combination NRT when compared with standard regimen [7]. This study intends to determine and gather further evidence about the effectiveness of preloading combination NRT among adult smokers of Kazakhstan.

**Research question:** What is the effectiveness of preloaded combination nicotine replacement therapy on smoking cessation?

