### 3. Methodology and ethical considerations

#### Objectives:

- To determine the effectiveness of preloaded combination nicotine replacement therapy (NRT) on smoking cessation of tobacco smokers.
- To determine the predictors of smoking cessation among the study participants.
- To determine the change in health-related quality of life due to smoking cessation.
- To determine the perception of treatment adherence among the study participants.

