#### Methodology:

**A. Trial Design:** This randomized, controlled, two-armed, single-blinded, superiority trial with 1:1 allocation ratio is designed based on CONSORT 2010 Guidelines. This superiority trial intends to gather further evidence that combination nicotine replacement therapy is more efficient than a fast-acting NRT alone.

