**G. Sample size:**

In a study conducted to find the efficacy of preloading combination NRT over standard combination NRT, 6-month sustained abstinence was 47.5% for the intervention group and 27.5% for the control group with a level of significance of 5%, power of 80% in the two-sided test [15.]. This proportion was considered to calculate the sample size for the current study. Eventually, the sample size was derived at 91 in each arm. By considering a loss to follow up of 10% in each arm, the sample size is 100.1 and hence rounded off conveniently to 100 per arm.

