| Nicotine Replacement Therapy for > 20 cigarettes per day                 | 
Nicotine Patch: Preloading for 4 weeks + 12 weeks post quit date
 
 
- 21 mg: 4 weeks before and after quit date
 
- 14 mg: Next 4 weeks
 
- 7 mg: Last 4 weeks
 
 
Nicotine chewing gums 4 mg for 12 weeks post quit date
(12/day on week 1.....1/day on week 12)
 | 
Nicotine Patch: 12 weeks post quit date
 
 
- 21 mg: 4 weeks after quit date
 
- 14 mg: Next 4 weeks
 
- 7 mg: Last 4 weeks
 
 
Nicotine chewing gums 4 mg for 12 weeks post quit date
(12/day on week 1.....1/day on week 12)
 |
| Nicotine Replacement Therapy for < 20 cigarettes per day                 | 
Nicotine Patch: Preloading for 4 weeks + 12 weeks post quit date
 
 
- 21 mg: 4 weeks before and after quit date
 
- 14 mg: Next 4 weeks
 
- 7 mg: Last 4 weeks
 
 
Nicotine chewing gums 2 mg for 12 weeks post quit date
(12/day on week 1.....1/day on week 12)
 | 
Nicotine Patch: 12 weeks post quit date
 
 
- 21 mg: 4 weeks after quit date
 
- 14 mg: Next 4 weeks
 
- 7 mg: Last 4 weeks
 
 
Nicotine chewing gums 2 mg for 12 weeks post quit date
(12/day on week 1.....1/day on week 12)
 |
| CO monitoring, Fagerstorm score, smoking frequency, medication adherence | 0-day, Month- 1, 3, 6, 9, 12                                                                                                                                                                                                                                                                                                                 | 0-day, Month- 1, 3, 6, 9, 12                                                                                                                                                                                                                                                                             |

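### Sections A and D describe combination NRT against gum alone with no preload, contradicting the preloaded versus standard combination comparison in section J, the budget and section 6

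*Protocol*

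**What the plan says.** **Gum-alone version.** Section A (Trial Design) states the superiority aim as showing that "combination nicotine replacement therapy is more efficient than a fast-acting NRT alone". Section D (Intervention and Control arm) gives the intervention arm a "fixed dose combination of nicotine patch and 4 mg nicotine chewing gum for 12 weeks" and then says: "The control arm includes 4 mg nicotine chewing gums alone for 12 weeks on tapering dosage pattern". Neither section mentions a preload, and section D gives 4 mg gum to everyone.

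**Preloading version.** In section J (Therapy protocol) the experimental column reads "Nicotine Patch: Preloading for 4 weeks + 12 weeks post quit date" and the control column "Nicotine Patch: 12 weeks post quit date". Both columns step the patch down through 21, 14 and 7 mg and give 12 weeks of gum after the quit date, at 4 mg above 20 cigarettes a day and 2 mg below 20.

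**The rest of the protocol.** The research question is "What is the effectiveness of preloaded combination nicotine replacement therapy on smoking cessation". The first objective is "To determine the effectiveness of preloaded combination nicotine replacement therapy (NRT) on smoking cessation of tobacco smokers". Section G takes its rates from a study of the "efficacy of preloading combination NRT over standard combination NRT". The Budget justification counts 120 patches over 16 weeks for the intervention group, 90 over 12 weeks for the control group, and 600 gums for each participant. Section 6 gives patches and gum to both groups and preloading to the experimental group.

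**The concern.** The two versions are different trials. In sections A and D the arms differ by the patch, so the trial estimates the benefit of adding a patch to gum. In section J the arms differ only by four weeks of patch before the quit date, so it estimates the effect of preloading. Only the second answers the research question.

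Three things depend on which text is followed:

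- **Treatment given.** A prescriber working from section D withholds patches from controls, gives nobody a preload, and gives 4 mg gum to smokers of 10 to 19 a day, who get 2 mg under section J.
- **Sample size.** Section G's rates are described as preloaded against standard combination NRT. They do not describe a gum-alone control, and the protocol gives no abstinence rate for one.
- **Review and reporting.** An ethics committee or reader relying on A and D would approve or report a trial different from the one scheduled and costed.

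**Working it through.** **1. The two definitions side by side**

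| | Sections A and D | Section J |
|---|---|---|
| Control patch | none | 12 weeks after quit date |
| Experimental patch | 12 weeks | 4 weeks before and 12 weeks after quit date |
| Gum strength | 4 mg for all | 4 mg or 2 mg by consumption |
| Difference between arms | the patch | the preload |

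A control of gum alone excludes a patch, so no reading reconciles the two columns.

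**2. Units per participant under section J**

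Assume one patch a day, and gum falling by one piece a day each week from 12 to 1. The protocol gives only the two ends of the gum taper.

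- Experimental patches: 16 × 7 = 112 (budget 120).
- Control patches: 12 × 7 = 84 (budget 90).
- Gum: 7 × (12 + 11 + … + 1) = 7 × 78 = 546 (budget 600).

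Each budgeted count covers the section J need with a small margin. Under section D the patch needs would be 12 × 7 = 84 and 0. The budget buys patches for controls and 16 weeks of them for the experimental arm, so it was built on section J.

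**3. The sample size in section G**

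Inputs from section G: p1 = 0.475, p2 = 0.275, two-sided 5%, 80% power. The mean proportion is 0.375. With pooled variance and no continuity correction:

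n = [1.960 × √(2 × 0.375 × 0.625) + 0.8416 × √(0.475 × 0.525 + 0.275 × 0.725)]² / 0.20²

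= [1.960 × 0.6847 + 0.8416 × 0.6699]² / 0.04 = (1.9057)² / 0.04 = 90.8, rounded up to 91 per arm.

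The stated 91 is reproduced, for the contrast that section G describes, which is section J's. No sample size can be derived for a gum-alone control, because the protocol gives no rate for it.

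**4. Cost check, supporting only**

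Prices from the Budget justification are USD 8 per patch, 0.35 per gum and 8 per cotinine kit, with four kits per participant. Take 100 per arm, from section G.

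- Section J: 120 × 8 × 100 + 90 × 8 × 100 + 600 × 0.35 × 200 + 4 × 8 × 200 = 96,000 + 72,000 + 42,000 + 6,400 = USD 216,400. This is 95% of the USD 228,400 line for materials and supplies.
- Section D (the budgeted 12-week count of 90 patches for the intervention arm, none for control): 72,000 + 42,000 + 6,400 = USD 120,400, or 53% of that line.

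The match depends on 100 per arm. Section C says 490 per arm, at which the section J items would cost USD 1,060,360 and the section D items USD 589,960. Neither fits the line. The per-participant counts in step 2 do not depend on the number of participants and are the firmer evidence.

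**The case against.** The best defence is that section J is the only part of the protocol with a usable regimen. Section D gives no patch strength, no step-down schedule and no gum count, so a prescriber would probably work from section J. Section D's silence on the preload is also an omission rather than a denial, since its 12 tapering weeks match the course after the quit date in section J. Both points are fair, and they make the wrong treatment less likely in practice. They do not help with the gum-alone control, section A's comparator or the universal 4 mg gum, which contradict section J directly.

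Some supporting points need limits:

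- The split of gum strength by consumption rests on section J alone. The budget and section 6 give no strengths.
- The Declarations promise the control group standard treatment after the trial. They do not say that it is withheld until then, and the term is not defined there. The sentence fits badly with section J but is not a clear contradiction.
- Reproducing 91 per arm shows that the arithmetic is right and which contrast was meant. It does not validate the planning rates, which are for 6 months while the primary outcome in section E is at 12 months.
- The section J row headings leave a smoker of exactly 20 a day, who is eligible under section C, without a defined gum strength. This is a minor gap affecting gum strength only.

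**Conclusion.** The contradiction is real and must be corrected. Sections A and D misstate the comparator and leave out the preload, and the rest of the protocol identifies section J as the intended design. At one patch a day, the difference is 84 against 0 patches for a control participant and 112 against 84 for an experimental participant. If section D were followed, the trial would not answer its own question and its planning rates would not apply. The conclusion rests on the text and the per-participant counts. It does not depend on the cost comparison, and the separate conflict between 100 and 490 per arm does not affect it.

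**What to change.** - **Section A:** state the aim as superiority of preloaded combination NRT over standard combination NRT.
- **Section D:** define control as patch (21, 14 and 7 mg, four weeks each) plus gum for 12 weeks after the quit date. Define intervention as the same regimen plus a 21 mg patch for the four weeks before the quit date. Set gum strength at 4 mg or 2 mg by daily consumption, as in section J.
- **Section J:** change one row heading, for example to 20 or more cigarettes a day, so that exactly 20 has a gum strength.
- **Declarations:** say that the control arm receives standard combination NRT during the trial.
- **Sections 6 and 7:** while editing, replace the stray term Afterload, which does not match the preloading regimen.

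The cost is protocol wording only. Section G's calculation, the patch schedules and gum counts in section J, and the drug budget do not change.
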